### Qualitative study

Focus groups will be conducted on each of the four wards with both patients and nurses in different sessions every six months. These group talks contain questions from a semi-structured interview based on the German version of the Ward Atmosphere Scale [30]. Answers and discussions will be audio-taped and evaluated. The acceptance of an open or closed ward management, the ward atmosphere depending on the door status, the feeling of safety and of stigmatization will be addressed. In weekly meetings, the ward team will reflect on problems or uncertainties in the context of the open-door policy during the past week. These meetings will be documented by taking notes. These meetings are thought to help categorize specific difficulties which can be addressed during the planning and implementation of intervention methods.

### Sample size

The size of the sample is equivalent to the total of all patients admitted to the respective hospitals’ acute care units in the intervention period. As an estimate, we expect an amount of 560 admissions per year at each ward in Tuebingen and 420 at each ward in Friedrichshafen. With three months baseline and 24 months of intervention, we expect 4410 patients in 27 months in total.

With regard to the qualitative part of the study, we estimate a total of 280 participants. This includes five times two focus groups with patients and two focus groups with staff separately, with each seven participants for all the four wards, in total 280 patients and 56 professionals.

### Randomization

In this study, no individual randomization is possible because conditions cannot be controlled equally. In the case of two basically identical acute wards, however, cluster randomization is feasible by means of a strictly alternating admission system to one of the two acute wards of the hospital. At baseline, units do not differ in terms of number of admissions, patients´ diagnoses, number or distribution of professional groups. Structural conditions are exactly identical.

### Data collection and management

Data on the door status with registration of reason, time, ID, diagnosis, legal status and explanatory statement will be documented by the nursing staff on a daily basis. Specific interventions for patients at risk during open-ward periods, time and duration, as well as qualitative data from weekly meetings and focus groups will be documented, recorded and transcribed by study staff. Quantitative data on bed occupancy, diagnoses and agreements on leaving the ward will be collected from in-house documentation systems. Data on restraint during survey period will be provided by the department of IT and medical controlling. Staffing levels for each day will be obtained from available nursing schedules.

### Statistical analysis

Calculations will be performed with SPSS.

Descriptive statistics will be obtained. Linear or logistic models for outcomes will be used to examine relationships between explanatory variables and outcomes over time.

For all tests, if necessary, measures will be transformed before analysis. All analyses are exploratory.

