**Methods:**

This study investigates whether indicators of an open-door policy, as measured by a priori determined outcomes, can be improved by a defined complex intervention on two intervention wards in two psychiatric hospitals, compared to two control wards with otherwise very similar conditions. Both hospitals contain two wards identical in structure and patient admittance policies, so that a similar study protocol can be followed with similar patient populations. Both hospitals have a defined catchment area and receive voluntary and involuntary admissions. In a baseline phase, wards will be opened facultatively (i.e., if it seems possible to staff). In the following intervention period, one ward per hospital will establish an enhanced open-door policy by applying additional strategic and personnel support. As a control group, the control ward will continue to be opened facultatively. After one year, control wards will be opened according to the open-door policy as well. Interventions will include the continuous identification of patients at risk as well as the development of individual care concepts and additional staffing. For this purpose, nursing and medical staff will be methodically supported on an ongoing basis by study staff.

Outcomes variables will be the percentage of door opening on each ward between 8 a.m. and 8 p.m., the percentage of all treatment days with the door opened and the number of involuntary treatment days with open doors. Data on frequencies of aggressive incidents, absconding, police searches, and seclusion or restraint will be used as control variables. Additional costs will be calculated.

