## Methods

This study aims to determine the extent to which a total of four wards in two psychiatric hospitals, where also involuntarily admitted patients are treated, can establish an open-door policy via additional staffing and strategic support. For this purpose, the same intervention is carried out in two psychiatric hospitals in Tuebingen and Friedrichshafen, where the two identical wards are either next to each other (Friedrichshafen), or on superimposed floors (Tuebingen). In both scenarios, one ward will serve as experimental, while the other will serve as control. The patients will be admitted in an alternating fashion. After one year, the ward which had previously been the control ward will receive the intervention. The intervention will be continued at the primary intervention ward. In the control wards, treatment as usual will take place. That is, ward doors will not stay closed throughout the first year but will be opened according to clinical considerations as has been previously practiced (so-called facultatively opened doors). After 12 months, the two control wards will undergo three months of implementation of the new policy and become intervention wards as well. Both hospitals provide similar conditions with identical ward architecture and an alternating patient admittance policy, so that the study can be carried out with the same study protocol and similar patient populations.

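### The policy is set ward by ward on four wards, but the named linear or logistic models make no provision for ward clustering or serial correlation

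*Protocol article*

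**What the plan says.** All references are to the protocol article.

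- **Level of the intervention.** The abstract describes a comparison "on two intervention wards in two psychiatric hospitals, compared to two control wards with otherwise very similar conditions". The Methods section says of the two hospitals: "In both scenarios, one ward will serve as experimental, while the other will serve as control". It adds a crossover: "After 12 months, the two control wards will undergo three months of implementation of the new policy and become intervention wards as well".
- **Outcomes.** Outcome measures names three primary quantities: percentage opening time between 8 a.m. and 8 p.m., the percentage of treatment days with the door open at least part of the time, and the number of involuntary treatment days with the door open. An open day with seven involuntary patients present counts as seven. Under Data collection and management, nursing staff record door status daily.
- **Groups and size.** Study participants defines the investigation and control groups as the patients treated on the respective wards in the first 12-month period. Sample size gives a head-count: "we expect 4410 patients in 27 months in total". It states no power, effect size or allowance for clustering.
- **Cluster language.** Randomization says that "cluster randomization is feasible by means of a strictly alternating admission system to one of the two acute wards of the hospital". Neither the sample size nor the analysis section takes this up.
- **Analysis.** The model statement is "Linear or logistic models for outcomes will be used to examine relationships between explanatory variables and outcomes over time". The software is SPSS, and the section closes with "All analyses are exploratory". It names no unit of analysis, ward or hospital term, or error structure.

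**The concern.** Two kinds of dependence are built into the design.

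First, all days and all patients on a ward share that ward's team, leadership, location and policy. There are only four wards to separate the effect of the policy from the effect of being that ward.

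Second, door status on consecutive days is unlikely to be independent. Under Standard care, opening depends on every patient accepting time agreements and on sufficient staff. On intervention wards, an at-risk patient is a stated reason to lock. Patients and staffing tend to carry over from one day to the next.

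A linear or logistic model in its standard form treats every row as independent. Applied to about 365 days or several hundred admissions per ward, it would credit the comparison with more information than it has. Confidence intervals would be too narrow and p-values too small for every primary outcome. The article says that it aims at robust data and at recommendations for guidelines, so the precision attached to its estimates matters.

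**Working it through.** **Step 1: the plan's own figure.** Sample size gives 560 admissions per year for each Tuebingen ward and 420 for each Friedrichshafen ward.

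(2 × 560 + 2 × 420) × 27/12 = 1960 × 2.25 = 4410.

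The stated figure reproduces exactly. It is a count of admissions and contains no design effect.

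**Step 2: inputs.**
- From the documents: 4 wards, 2 per arm; mean admissions per ward per year (560 + 420)/2 = 490; a parallel year of about 365 days per ward.
- Assumed, because the documents give none: the ward-level intraclass correlation (ICC) and the day-to-day autocorrelation ρ, taken as AR(1).

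**Step 3: formulas.**
- Clustering: DE = 1 + (m − 1) × ICC, with m = 490 admissions or 365 days.
- Serial correlation over n = 365 days: DE = (1 + ρ)/(1 − ρ) − 2ρ(1 − ρⁿ)/[n(1 − ρ)²].
- Ratio of true to naive standard error = √DE.
- Actual rejection rate of a nominal 5% test with no effect = 2 × [1 − Φ(1.96/√DE)].

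Examples: with ICC 0.01 on admissions, DE = 1 + 489 × 0.01 = 5.89 and √DE = 2.43. With ρ = 0.9, DE = 19 − 0.49 = 18.51 and √DE = 4.30.

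**Step 4: results for the parallel year.**

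| Assumption | DE | SE ratio | Actual type I error |
|---|---|---|---|
| Days, ρ = 0.1 | 1.22 | 1.11 | 8% |
| Days, ρ = 0.3 | 1.85 | 1.36 | 15% |
| Days, ρ = 0.5 | 2.99 | 1.73 | 26% |
| Days, ρ = 0.7 | 5.62 | 2.37 | 41% |
| Days, ρ = 0.9 | 18.51 | 4.30 | 65% |
| Days, ICC 0.001 | 1.36 | 1.17 | 9% |
| Days, ICC 0.01 | 4.64 | 2.15 | 36% |
| Days, ICC 0.05 | 19.2 | 4.38 | 66% |
| Admissions, ICC 0.001 | 1.49 | 1.22 | 11% |
| Admissions, ICC 0.01 | 5.89 | 2.43 | 42% |
| Admissions, ICC 0.05 | 25.45 | 5.04 | 70% |

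At ICC 0.01 the 1960 admissions of the parallel year carry the information of about 1960/5.89 = 333. At ICC 0.05 the figure is about 77.

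**Step 5: does using the baseline and the crossover remove the problem?** Daily data for four wards were simulated with no policy effect, 1,500 data sets per setting, and analysed by ordinary least squares in two ways:
- (a) the parallel year with a hospital term;
- (b) 120 + 365 + 365 days (baseline, parallel year, all wards open-door) with ward and phase fixed effects.

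The ICC here is the share of variance due to shifts specific to a ward in a phase. Constant ward differences would be absorbed by the ward terms in (b).

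| ρ, ICC | (a) type I error | (b) type I error |
|---|---|---|
| 0, 0 | 5% | 6% |
| 0.5, 0 | 27% | 27% |
| 0.5, 0.01 | 45% | 44% |
| 0.5, 0.05 | 68% | 66% |

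With independent data both models behave properly. With dependence, ward and phase terms alone do not restore the nominal level.

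**Step 6: what four wards can support.** An analysis of ward means in the parallel year leaves 2 residual degrees of freedom, or 1 with a hospital term; the critical t values are 4.3 and 12.7. Exchanging the two wards within each hospital gives 2 × 2 = 4 arrangements, so the smallest two-sided exact p-value for that year is 2/4 = 0.5.

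**The case against.** The strongest reply is that the article does not state the model being criticised. It names a family of models without a unit or covariance structure. A linear mixed model with AR(1) errors belongs to that family and can be fitted in SPSS. A condensed article may leave such detail to a fuller document that is not shown. This stands in part: the independent-observation reading is an inference. It is nevertheless the natural one, because groups and size are framed in patients and the cluster language is not carried into the analysis.

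A second reply is that the plan says "All analyses are exploratory" and sets no alpha or power. That limits confirmatory claims but does not correct a standard error or a confidence interval.

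Several stronger readings are tempting but not supported:

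- *That the policy varies only between wards.* All wards have a baseline phase and the control wards cross over, so there is also contrast within wards. The p-value floor of 0.5 applies only to the parallel year.
- *That standard errors will be far too small.* No correlation is given. At the low end the understatement is slight, and the article also describes locking as temporary and situational.
- *That patients sharing one door status will be entered as independent rows, multiplying the error further.* The seven-patient example defines a count and does not prescribe an analysis. The 4410 is likewise a head-count, not a declared unit of analysis.
- *That chance drift will be reported as an effect.* Nothing in the article says how results will be reported.

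**Conclusion.** The point holds in a bounded form. The policy is set by ward on four wards and the primary outcomes are daily ward quantities, while the named models make no provision for either kind of dependence. Fitted in their standard form to days or admissions, they understate standard errors at every positive correlation examined.

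Over the assumed range, the factor runs from about 1.1–1.2 to about 4–5, and the actual type I error from about 8–11% to 65–70%. The direction is secure provided the correlation is positive. The size is not known from the documents, and the whole range is conditional on independent-observation models being fitted, which the article implies but does not state. The exploratory label and the crossover do not remove the problem. The wording should be settled before any interval or p-value for the policy effect is reported.

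**What to change.** In the Statistical analysis section:

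1. Name the ward as the unit of intervention.
2. Analyse the door outcomes as ward-day or ward-week series, with ward terms and calendar-time or phase terms that use the baseline and crossover periods, and with AR(1) or HAC errors. AR(1) errors are available in the SPSS mixed-model procedure.
3. Report the within-hospital contrast for each hospital separately, then the average.
4. Give no patient-day or admission-level p-values for the policy effect on door outcomes.
5. State that, with two wards per arm, between-ward contrasts describe these four wards. This includes contrasts for patient-level events such as absconding or coercive measures.

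Item 5 is needed because items 1 to 4 are only a partial repair. Autocorrelation-adjusted errors do not capture lasting shifts specific to one ward, and cluster-robust or random-ward methods are unreliable with four clusters.

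The cost is analysis wording only, with no new data. Intervals will be wider and the claims more modest.

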### Qualitative data

Thematic analysis will be used for identifying, analyzing and reporting themes or patterns within data. The interviews will be transcribed verbatim and analyzed according to Mayring [31]. This content analysis technique is broadly applied in social sciences to evaluate large quantities of material from semi-structured interviews. It allows to build categories of content and to count certain text components (e.g. aspects of stigmatization, safety feeling, ward atmosphere).

## Discussion

Acute psychiatric care units are often locked in order to prevent the absconding of patients at risk. However, even under the good conditions of hospital treatment in Germany (with more beds available than in many other countries), this classification only applies to about 10% of patients treated in said units. Thus, about 90% of patients are treated on a voluntary basis. Though some of the patients treated voluntarily are at risk of suicide, too, and some of them suffer from serious symptoms, most of them are treated at wards with locked doors without the therapeutic need or legal requirements to do so. Literature offers numerous suggestions on interventions and structural changes in the treatment of acute psychiatric patients. So far, evidence is scarce and focuses on opinions or refers to observational studies.

This study aims to investigate the impact of an open-door policy in a prospective quasi-experimental design on adverse events such as absconding, suicides, suicide attempts, severe self harm and aggressive incidents as well as costs and limitations. More evidence is needed to identify criteria and to develop interventions to modify common treatment methods to a less restrictive, more open and supportive psychiatric care. It is the first prospective controlled study with a quasi-experimental design on this topic.

The results are expected to make a significant contribution to providing sustainable, comprehensive and evidence-based treatment recommendations for acute psychiatric care units and to provide substantial evidence instead of beliefs for a highly controversial discussion.
